### Design of the RCT

A brief structured summary of the RCT part of the Promoting Aging Migrants’ Capabilities Study is provided in Table 2.

**Table 2 Tab2:** **A brief structured summary of the RCT part of the promoting aging migrants’ capabilities study**
*****

**Data category**	**Information**
Primary registry and trial identifying number	ClinicalTrials.gov NCT01841853
Date of registration in primary registry	10 April 2013
Secondary identifying numbers	-
Source(s) of monetary or material support	The Swedish Research Council, the Centre for Person-Centred Care (GPCC) at Gothenburg University, Sweden
Primary sponsor	The University of Gothenburg, Sweden
Secondary sponsor(s)	The City of Gothenburg, Sweden
	The Region of Västra Götaland, Sweden
Contact for public queries	[name], [name]
Contact for scientific queries	[name], [name], the Sahlgrenska Academy at the University of Gothenburg, Institute of Neuroscience and Physiology/Section for Health and Rehabilitation, Sweden
Public title	The Promoting Aging Migrants’ Capabilities Study
Scientific title	The Promoting Aging Migrants’ Capabilities Study: a person-centred approach to health promotion for persons 70+ who have migrated to Sweden
Countries of recruitment	Sweden
Health condition(s) or problem(s) studied	Health promotion for older persons born abroad
Intervention(s)	Intervention: 4 senior meetings and 1 follow-up home visit
	Control: Conventional care and follow-up
Key inclusion and exclusion criteria	Ages eligible for study: ≥ 70 years; Sexes eligible for study: both; Accepts healthy volunteers: Yes
	Inclusion criteria: adult person (≥70 years); born in Finland or any of the four countries in the Balkan Peninsula; living in an urban district in a medium-sized city; living in ordinary housing; not dependent on informal or formal help in daily activities
	Exclusion criteria: impaired cognition [Mini Mental State Examination (MMSE) below 80% of administered items]
Study type	Interventional
	Allocation: randomised; Intervention model: parallel assignment; Masking: non-blind
	Primary purpose: Health promotion
	Phase III
Date of first enrolment	08 August 2012
Target sample size	130
Recruitment status	Recruiting
Primary outcome	Activities of Daily Living (ADL)
Key secondary outcomes	Frailty indicators, falls and fear of falls, symptoms, depression, healthcare consumption, self-rated health, life satisfaction, leisure activities, assistive technology, and social support

*WHO Trial Registration Data Set.

#### Study population

The intention is that the study group should comprise as representative a sample as possible of older persons in the urban district who have migrated to Sweden. For pragmatic reasons, particularly considering the need for language resources, we chose to include persons from two of the largest immigrant groups in the targeted urban district, one Nordic country (Finland) and one European region (the Balkan Peninsula, including the countries Bosnia-Herzegovina, Croatia, Montenegro, and Serbia, the populations who share their mother tongue). Persons eligible for the RCT must therefore comply with all of the following criteria for randomisation: born in Finland or any of the selected four countries in the Balkan Peninsula (Bosnia-Herzegovina, Croatia, Montenegro, and Serbia); 70 years of age or older; living in ordinary housing in the urban district; and not dependent on informal or formal help in daily activities. The only exclusion criterion is impaired cognition (Mini Mental State Examination (MMSE) below 80% of administered items [41]).

#### Outcomes

Activities of daily living (ADL) is the primary outcome measure [42,43]. Secondary outcome measures are: physical frailty indicators (mobility, strength, balance, cognition, nutrition, fatigue, physical activity, and visual impairment), falls and fear of falls, symptoms, depression, healthcare consumption, self-rated health, life satisfaction, leisure activities, assistive technology, and social support. The outcomes have, to a large extent, been tested for validity and reliability. All outcome measures are to be assessed at baseline and at the 6- and 12-month follow-ups. Details are provided in Table 3.

**Table 3 Tab3:** **Outcome measurements and follow-ups in the RCT part of the promoting aging migrants’ capabilities study**

**Primary outcome**	**Measurement**	**T0**	**T1**	**T2**
		**baseline**	**6-months**	**12-months**
Activities of Daily Living (ADL)	The ADL-staircase	X	X	X
**Secondary outcome**	**Measurement**			
Fatigue	The Mob-T scale	X	X	X
Grip strength	North Coast-dynamometer	X	X	X
Physical activity	Questionnaire	X	X	X
	Physical and domestic activity scale	X	X	X
Balance	The Berg balance scale	X	X	X
Gait speed	Four-meter walking test	X	X	X
Weight loss	The Göteborg Quality of Life Instrument	X	X	X
Cognition	Mini Mental State Examination (MMSE)	X	X	X
Visual impairment	KM-visual acuity chart	X	X	X
Falls	Questionnaire	X	X	X
Fear of falls	Questionnaire	X	X	X
Symptoms	The Göteborg Quality of Life Instrument	X	X	X
Depression	GDS 20	X	X	X
Healthcare consumption	Register data	X	X	X
Self-rated health	SF 36 (one question)	X	X	X
Life satisfaction	Fugl-Meyer -LiSat	X	X	X
Participation/Leisure activities	Questionnaire	X	X	X
Assistive technology	Questionnaire	X	X	X
Social support	Questionnaire	X	X	X

#### Recruitment, participant timeline, and randomisation

The results of the pilot study preceding this full-size RCT ([name], [name], [name]: Unpublished observations) indicated that the recruitment procedure described in the original protocol for the senior meetings [24] needed to be adjusted to be more effective. Therefore, a plan consisting of three waves of recruitment strategies was adopted. The waves are hierarchical and an appropriate wave was to be added if an antecedent wave was unsuccessful in reaching the target number for inclusion. The first wave implies that participants are drawn at random from official registers in the urban district. All addresses, equally divided between the populations (Finland and the four countries in the Balkan Peninsula), are listed in random order (two separate lists). Based on the sampling lists, participants will be consecutively included in the study until the decided sample size is reached (n≥65 from each population). Letters will be sent to all randomly selected persons asking them to participate in the study. Invited participants also receive a description of the study, how it is to be conducted, and what is expected of those consenting to participate. The letter stresses the fact that participation is voluntary; it is followed by a telephone call about 1–2 weeks later. If no telephone number is to be found in public records, a second letter with a request to make contact by telephone is sent. During the call, the persons will be informed verbally about the study and given the opportunity to ask questions if anything is unclear. They are also asked personally if they would like to participate, while again stressing that participation is voluntary. Everyone who fulfils the criteria for inclusion and decides to participate is randomised by the research assistant after baseline assessment to one of the two groups using sealed, opaque envelopes prepared by an unattached researcher. Participants living together in the same household are allocated to the same group. Wave two is identical to wave one but involves an expansion of the targeted area to also include another adjacent urban district with similar demographics. Finally, wave three entails word-of-mouth promotion through one-chain snowballing [44]. This strategy uses former study participants and key persons in the aforementioned reference groups to facilitate spreading information about the study. Interested persons fulfilling inclusion criteria are invited to contact the operative group for further information and to undergo baseline assessment when appropriate. The third wave also includes local radio station advertisements containing brief information in the participants’ mother tongue on the study and how to contact the operative group. A detailed overview of the planned flow of participants is provided in Figure 1.

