#### Masking (blinding)

Because of the nature of the intervention, neither participants nor the professionals in the urban district can be blinded to allocation in the RCT. In addition, supported by the pilot study results, assessors cannot be blinded since we need to match assessors and participants linguistically. Finally, we also assume that there would be less attrition if the participants could meet the same assessor at most of the follow-ups.

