#### Power calculation

The power calculation was based on results gained in the preceding study ‘Elderly Persons in the Risk Zone’ [24], using the Berg balance scale as a basis. The Berg balance scale is one of the secondary outcome variables (range 0–56), with assumed mean values for the intervention and control groups of 32 and 28, respectively (15% difference), and a standard deviation of 8 in both groups. To be able to detect a significant difference between the two groups in a two-sided test with a significance level of 0.05 and 80% power, we need at least 65 persons in each group. Therefore, a total of at least 130 persons will be included.

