#### Data management

All participant information, including informed consent forms, interviews on audio files, etc., will be stored separately from study records identified by code number in locked file cabinets in areas with limited access. The original data collection forms are to be stored in numerical order in a secure and accessible place and manner for a period of 10 years after completion of the study. An external research assistant will enter data into the computer and also perform quality control of the database. During and after the study completion, the research group will have access to the full database. Any modifications to data written to the database will be documented in a log book linked to the database. Regular back-ups of the database will be undertaken automatically by the university’s information technology department. The main database, as well as local databases, will be secured with password-protected access systems.

No data monitoring committee will be needed since risks in connection with this study are minimal, there is a fixed target figure for included participants, and no interim analyses are planned. Even so, the research group, and ultimately the research leader, will be responsible for database security and quality.

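### Country-of-birth population is the sampling stratum, yet it enters the between-arm analysis only if observed baseline differences prompt adjustment; it should be a pre-specified factor

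*Protocol article*

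**What the plan says.** **Sampling.** Under Recruitment, participant timeline, and randomisation, addresses are split equally between the two populations and put in random order on two lists. From these, "participants will be consecutively included in the study until the decided sample size is reached (n≥65 from each population").

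**Allocation.** The same section describes opaque sealed envelopes made up by an independent researcher, with members of one household going to the same arm. It mentions no strata, blocks or ratio.

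**Assessment.** Under Masking (blinding), "assessors cannot be blinded since we need to match assessors and participants linguistically".

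**Sample size.** Under Power calculation, the Berg balance scale, a secondary outcome, is used with "assumed mean values for the intervention and control groups of 32 and 28, respectively (15% difference"). Each arm is taken to have an SD of 8, and the comparison is planned as a two-sided 0.05-level test at 80% power. From this, "we need at least 65 persons in each group". The section concludes: "Therefore, a total of at least 130 persons will be included".

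**Analysis.** Statistical analyses provides for adjustment when baseline differences between the arms make it seem needed. It names no covariate, fixes no subgroup analysis, and assigns ordinal outcomes to non-parametric methods.

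**The concern.** Population is built into the design. Each has its own list, its own quota and its own mother tongue, and language matching means that population and assessor will largely go together. A variable of this kind is normally fixed in the analysis beforehand. Here its use depends on the data, which has two consequences.

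- If the arms happen to be balanced on population, the rule gives no reason to adjust. Any outcome difference between the populations, and between the assessors matched to them, then stays in the residual variance and widens the interval for the arm effect.
- If the arms are not balanced, someone must decide whether the imbalance is large enough to matter. The trial is unblinded, and under Data management the research group can see the full database while the study runs. The decision could therefore be taken with the outcomes in view.

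A standard two-group rank test does not solve this. It has no place for population unless a stratified form is specified. This would affect the primary outcome, the ADL-staircase, if that is analysed as ordinal.

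**Working it through.** **1. The plan's own figure.** Inputs from Power calculation: difference 32 − 28 = 4, SD 8, two-sided 0.05, power 80%.

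n per arm = 2 × (1.960 + 0.842)² × 8² / 4² ≈ 62.8, so 63 (64 with the t distribution). The stated 65 is reproduced to within two. At 65 per arm the standard error is 8 × √(2/65) = 1.40, and power is Φ(4/1.40 − 1.96) = 81.3% (80.8% with the t distribution).

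**2. What the two figures of 65 secure.** Two arms of 65 make 130, and two populations of 65 make 130. These are the two margins of one 2×2 table, so the total does not conflict. A quota by population does not by itself fix the arm sizes. Under simple randomisation of 130, an exact 65:65 split has probability 7%, and the smaller arm falls below 60 with probability 33%. The cost in power is small: 81.1% at 60:70 and 80.4% at 55:75.

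**3. Chance imbalance on population if allocation is unstratified.** With 65 per population:

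| Difference in population share between arms | Simple randomisation | Arms fixed at 65:65, unstratified |
|---|---|---|
| more than 10 points | 25% | 29% |
| more than 15 points | 10% | 8% |
| 20 points or more | 3% | 3% |

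These figures ignore same-household allocation, which would raise them somewhat. If the populations differ by D points, an imbalance of s in share moves the crude contrast by s × D. With D = 4 assumed, 10 points of imbalance moves it by 0.4 Berg points and 20 points by 0.8.

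**4. Variance left in the error term.** In a 50:50 mix, a population difference D adds D²/4 to the variance. The documents do not give D, so 2 to 8 Berg points is an assumed range. They also do not say whether the SD of 8 already contains this variance, so both cases are shown, with 65 per arm and the normal approximation.

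| D | SD 8 includes population variance: unadjusted → adjusted power | SD 8 is within population: unadjusted → adjusted power | n per arm needed unadjusted (second case) |
|---|---|---|---|
| 2 | 81.3% → 81.9% | 80.7% → 81.3% | 64 |
| 4 | 81.3% → 83.7% | 79.0% → 81.3% | 67 |
| 6 | 81.3% → 86.8% | 76.1% → 81.3% | 72 |
| 8 | 81.3% → 90.8% | 72.2% → 81.3% | 79 |

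Example for D = 4, where D²/4 = 4. In the first case the adjusted SD is √(64 − 4) = 7.75. In the second the unadjusted SD is √(64 + 4) = 8.25.

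**The case against.** The strongest reply is that this is a condensed article. Strata, blocks and covariate lists commonly sit in a full protocol or analysis plan that is not shown, and the participant-flow figure is missing. Adjustment for observed baseline differences could include country of birth. Chance imbalance under randomisation is not bias, and the type I error rate already allows for it: a shift of 0.4 points is under 0.3 of the standard error of 1.40. No outcome difference between the populations is reported, and language preference need not follow birth country. All the figures concern a secondary outcome. If change from baseline is compared, a constant difference in level between the populations cancels, and the relevant D could be smaller.

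Most of this stands, and it limits the point. It does not answer the rule that the article does state. That rule decides when adjustment happens, and it does so from the data.

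A reader might infer more than the text supports:

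- **That the per-arm 65 was misapplied as a population quota.** Both give 130, and an even split by population is a legitimate sampling target.
- **That all envelopes came from one unstratified set.** The article is silent, and a set per list is not excluded.
- **That a minimum quota contradicts the remark under Data management that "there is a fixed target figure for included participants".** That sentence explains why no data monitoring committee is planned; the difference is one of wording.
- **That population is the strongest prognostic factor.** No outcome data by population are given.

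**Conclusion.** The point holds for the analysis rule. Population defines the sampling, but whether it enters the analysis is left to the observed baseline differences. That forgoes precision when the arms are balanced and invites a post-hoc choice when they are not.

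The size is uncertain and probably modest. On the Berg scale, power changes by 0.6 percentage points at D = 2. At D = 8 it changes by about 9 points, either as a gain forgone (81.3% to 90.8%) or as a loss (81.3% to 72.2%). If the SD of 8 already includes population variance, planned power is not reduced and only the gain is missed. The 25–29% chance of an imbalance above 10 points applies only if allocation is unstratified. Nothing can be computed for ADL from the article. The change is worth making because it uses a variable already held on every participant and costs very little.

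**What to change.** 1. In Statistical analyses, for population, replace the data-dependent trigger with a commitment: country-of-birth population (Finland or Balkan) is a factor in every between-arm comparison, whatever the baseline table shows. Where an outcome is analysed non-parametrically, use a rank test stratified by population, such as van Elteren's, in place of the simple two-group test.
2. Record this before any between-arm outcome analysis. The planned timeline lists data analyses from the second half of 2014, so the decision should be dated.
3. As clarification only, state that 65 per arm and 65 per population are separate margins of the total of 130, and say whether the envelopes are stratified by population.

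The cost is a little more analysis work and a stratified test instead of the simplest one. No participants are added, and a running allocation need not be changed.

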**Table 1 Tab1:** **Themes from the booklet used in senior meetings in the promoting aging migrants’ capabilities study**

**Themes from the booklet**	**Principal professional** *****
Aging	PT
Physical activity helps keep you physically fit	PT
Food is a prerequisite for health	PT
You can take care of problems with your health	RN
How to use medicines	RN
To cope with everyday life	OT
You do not need to feel insecure	OT
Technology in everyday life	OT
Will I lose my memory?	OT
Life events and quality of life during aging	SW
Anyone who needs help can get help	SW

*Physiotherapist (PT), registered nurse (RN), occupational therapist (OT), and social worker (SW).

The senior meetings are conducted by an operative group consisting of professionals employed in the urban district: an occupational therapist, a registered nurse, a physiotherapist, and a social worker. All professionals receive education and training on the programme content, and on leading groups prior to study commencement. The programme comprises four weekly senior meetings in small groups (four to six participants), in addition to an individual follow-up home visit two to three weeks after the last senior meeting. Having groups enables the possibility of peer education with participants learning from each other [39], and a person-centred approach increases the possibilities for participants to be seen as experts on their own situation [40]. Respect for the participant and his/her values and giving each participant the opportunity to maintain and develop his/her control over his/her own everyday activities, is essential in the meetings.

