#### Statistical analyses

Analyses of intervention outcomes and change over time will be made on the basis of the intention-to-treat principle, which means that participants will be analysed on the basis of the group to which they were randomised [45]. Standard adjustment of analyses according to eventual differences between groups at baseline will be made if necessary. After a thorough examination of the characteristics of collected data, the research group will consider different options for handling missing data. One possibility is the imputation method used in the preceding study ‘Elderly Persons in the Risk Zone’ [25,26], where a missing value was imputed with a value based on the median change of deterioration (MCD) between two measuring points (baseline and respective follow-up) of all those who participated at both measuring points. However, other methods of handling missing data will also be considered, and a final decision will be made by the lead researcher in consultation with a renowned statistician. Regardless of the method chosen, sensitivity analyses will be performed to compare the results to complete case analyses [46]. Although it is desirable, no subgroup analyses are predetermined. Instead, a valuation of the quality of collected data will determine if and which of these analyses are possible. Both descriptive and analytical statistics will be used to compare the groups and to measure change over time. Non-parametric statistics will be used in all cases where ordinal data are to be analysed; otherwise, parametric statistics will be used. A *p-*value of 0.05 or less will be considered significant. Statistical analyses will be performed using IBM SPSS Statistics for Windows, Version 22.0 (Armonk, NY, USA: IBM Corp. Released 2013).

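### Neither the sample size nor the analysis described allows for co-residents being randomised together or for the intervention being delivered in small groups

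*Protocol article*

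**What the plan says.** The section on recruitment, participant timeline and randomisation has participants randomised by sealed envelope after baseline assessment, with one exception: "Participants living together in the same household are allocated to the same group".

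The Intervention section (text after Table 1) describes "four weekly senior meetings in small groups (four to six participants") followed by an individual home visit, and gives learning from one another as a reason for the group format. Controls get conventional care, so no meeting groups exist in that arm.

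The Power calculation uses the Berg balance scale, a secondary outcome, taking means of 32 and 28. The spread is put at "a standard deviation of 8 in both groups". For a two-sided 5% test at 80% power it concludes that "we need at least 65 persons in each group". It mentions no ICC, design effect or household allowance.

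The Statistical analyses section commits to intention to treat and to adjustment for baseline differences where needed. On method it says: "Non-parametric statistics will be used in all cases where ordinal data are to be analysed; otherwise, parametric statistics will be used". It names no specific test or model and mentions neither household nor meeting group.

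**The concern.** The protocol creates two kinds of dependence between participants.

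- **Household.** This comes from the allocation itself and affects both arms. Two people who share a home and an allocation carry less information about the arm difference than two people randomised separately, if their outcomes are positively correlated. This is so whether or not the programme works.
- **Meeting group.** This comes from delivery and affects one arm only. It matters only if attending together makes outcomes within a group more alike, for example through peer learning or differences between groups in how the programme is led.

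An ordinary two-group comparison of persons ignores both. Under positive ICCs its standard errors are too small and its type I error exceeds 5%. Separately, a sample size calculated for independent persons overstates the power available at a true 5% level.

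**Working it through.** **Inputs from the Power calculation:** difference 32 − 28 = 4, SD 8, two-sided 0.05, power 80%, 65 per arm.

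**Reproducing the stated size.** With independent persons, n per arm = 2 × [8 × (1.960 + 0.842) / 4]² = 62.8, so 63. The t-test needs 63.8, so 64. Power at 65 per arm is 81.3% (normal) or 80.8% (t-test). The stated 65 is therefore the individual-level formula with one or two persons per arm to spare. The design effect that uses up this reserve is 65/63 ≈ 1.03 (65/63.8 ≈ 1.02 on the t-test).

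**Assumed inputs (none is in the documents):** f, the share of participants in co-resident pairs; ρ, the household ICC; ρg, the meeting-group ICC. The group size m of 4 to 6 is from the protocol and gives about 65/6 ≈ 11 to 65/4 ≈ 16 groups.

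**Formulas**
- Control arm: DE0 = 1 + fρ
- Intervention arm: DE1 = 1 + fρ + (m − 1)ρg
- True standard error: 8 × √(DE1/65 + DE0/65)
- Needed per arm: 31.4 × (DE1 + DE0), where 31.4 = [8 × (1.960 + 0.842) / 4]²
- Power: Φ(4/SE − 1.960)
- Type I error of an unadjusted test: 2 × [1 − Φ(1.960/R)], where R = √[(DE1 + DE0)/2] is the factor by which the unadjusted standard error is too small

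**Both sources together**

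| Case | f | ρ | m | ρg | DE1 | DE0 | Needed per arm | Power at 65 | R | Unadjusted type I error |
|---|---|---|---|---|---|---|---|---|---|---|
| Low | 10% | 0.1 | 4 | 0.01 | 1.04 | 1.01 | 65 | 80.4% | 1.012 | 0.053 |
| Middle | 20% | 0.3 | 5 | 0.05 | 1.26 | 1.06 | 73 | 75.4% | 1.077 | 0.069 |
| Extreme | 50% | 0.5 | 6 | 0.10 | 1.75 | 1.25 | 95 | 64.3% | 1.225 | 0.11 |

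Middle case in full: SE = 8 × √(2.32/65) = 1.511; 4/1.511 − 1.960 = 0.687; Φ(0.687) = 75.4%.

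**Household alone** (the part that does not depend on how delivery acts), with the same f and ρ:

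| Case | DE in both arms | Needed per arm | Power at 65 | Unadjusted type I error |
|---|---|---|---|---|
| Low | 1.01 | 64 | 81.0% | 0.051 |
| Middle | 1.06 | 67 | 79.1% | 0.057 |
| Extreme | 1.25 | 79 | 72.2% | 0.080 |

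The power figures are at a true 5% level. An unadjusted test would reject somewhat more often, but only because it does not hold 5%.

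**The case against.** The strongest reply has four parts.

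1. **The text names no test.** A reader might infer that the planned tests treat all 130 people as independent and that the confidence intervals are certain to be too narrow. The documents do not say so: the analysis section gives no model and states no independence assumption, and a cluster term may sit in a fuller plan that is not shown. This stands, so the statement about standard errors is conditional. It does not clear the power calculation, which is set out in full and reproduces without a design effect. Nor does it change the fact that the analysis, followed as described, would ignore the unit by which co-residents are randomised.

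2. **The effect may be negligible.** Both members of a pair must meet the age, birth-country, independence and cognition criteria, and both must consent. Nothing in the documents supports a particular share of pairs. In the low case 65 per arm still suffices on the normal approximation. This stands, which is why the low case is shown.

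3. **Meeting groups are not randomised units.** If delivery creates no correlation within groups, they cause no inflation. This stands; the household-only figures are the part free of that condition.

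4. **Concealment.** A reader might infer that a second household member could enrol later with an allocation already known. The protocol describes no such late entry, and it randomises after baseline with sealed, opaque envelopes. The possibility follows from the household rule, but it is neither stated nor quantified. It justifies a simple safeguard and is not evidence of bias.

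**Conclusion.** The point holds as a moderate one. Household is the unit of randomisation for co-residents in both arms, and meeting groups exist in one arm. The sample size allows for neither and has almost no reserve, and the analysis as described accounts for neither.

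Two consequences should be kept apart. The stated 80% power is overstated at a true 5% level, whichever analysis is used, once the average design effect passes about 1.03. Standard errors are too small only if the analysis carries no cluster term and the ICCs are positive. Across the assumed range, power runs from 80.4% through 75.4% to 64.3%, and unadjusted type I error from 0.053 through 0.069 to 0.11. The upper end needs many pairs and large ICCs, and its meeting-group part needs correlation produced by delivery.

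The power figures concern Berg balance. They say nothing direct about power for the primary outcome, activities of daily living.

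**What to change.** - **Household, both arms.** Account for household clustering with cluster-robust or GEE standard errors, or a random intercept. For outcomes treated as ordinal, use an ordinal model with the same allowance or a rank test for clustered data, in keeping with the non-parametric commitment.
- **Meeting group, intervention arm only.** Add a partially nested term, at least as a sensitivity analysis, with a small-sample correction because there are only about 11 to 16 groups. A single design effect common to both arms would not describe this.
- **Power.** Restate power at 65 per arm over a stated range of design effects, without enrolling more.
- **Allocation.** For households still to be randomised, open one envelope per household after all consenting members have completed baseline. This cannot reach those already enrolled.
- **Analysis set.** Keep every randomised person in the intention-to-treat analysis. Any exclusion of co-residents who joined later should be a sensitivity analysis only.

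**Cost:** household and meeting-group identifiers must be recorded (the documents do not say whether they are), intervals become slightly wider unless clustering is heavy (factor R above), and the stated power becomes less favourable. The analysis wording can be settled at any time before the data are analysed.
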